#### Ethics

2.2.5

The study will strictly adhere to established ethical standards, including the principles outlined in the Declaration of Helsinki (39) and the Ethical Principles of Psychologists and Code of Conduct of the American Psychological Association (40). In compliance with European and Spanish data protection regulations—specifically the General Data Protection Regulation (GDPR) (41) and the Spanish Organic Law 3/2018 on the Protection of Personal Data and guarantee of digital rights (42)—the study has been approved by the Research Ethics Committee of the University of Santiago de Compostela (Code: USC-003/2026-H). All personal data will be anonymized, securely stored, and accessible only to authorized personnel. Participation in the study will be entirely voluntary, without any financial or material incentives, and written informed consent will be obtained from all participants before involvement. Participants will be explicitly informed of their right to withdraw from the study at any time without penalty.

Suicide risk and acute distress will be assessed at each assessment point (T1, T2, and T3) using the Columbia–Suicide Severity Rating Scale Screen Version (C-SSRS Screen Version) (43). Positive responses indicating active suicidal behaviors will trigger the study safety protocol, including brief risk assessment by a trained psychologist, referral to the Psychological Care Unit of the University of Santiago de Compostela or emergency psychiatric services when needed, and exclusion or discontinuation from the intervention when acute risk is identified. The app will not collect diagnostic risk data or trigger automated risk alerts, but it will include a permanent “Help & Support” section with emergency contact information. Safety data and distress-related dropouts will be monitored monthly by the two senior clinical psychology supervisors. Adverse events will be documented and reported to the Research Ethics Committee.

Furthermore, participants assigned to the waiting list control group will be granted access to the app-based intervention after the study concludes. Any substantial modifications to the protocol will require prior approval from the relevant ethics committee before implementation.

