#### Eligibility criteria

2.2.2

Inclusion criteria include: (a) being an actively enrolled university student at the University of Santiago de Compostela (USC); and (b) having access to a smartphone with an internet connection. Exclusion criteria include: (a) having a current diagnosis of severe psychiatric disorder, including major depressive disorder with psychotic features, bipolar disorder, schizophrenia, severe cognitive impairment, dissociative disorders, active substance dependence, or active suicidal behaviors; (b) having started psychological or psychopharmacological treatment within the two months prior to the study or participating in another mental health-related study; (c) having insufficient proficiency in Spanish, or presenting sensory, cognitive, or physical impairments that would prevent engagement with the intervention; or (d) planning to move out of Galicia within the next 12 months.

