##### PPIA+M – App-based intervention plus multiconference group support

2.2.6.2

Participants assigned to this condition will receive the same five-week mobile intervention as those in the PPIA group, with the addition of a weekly 30-minute telephone-based multiconference session. These sessions will be conducted in small groups (5–6 participants) and facilitated by licensed psychologists or doctoral students trained in group interventions. At the beginning of the first telephone multiconference session, facilitators will explain confidentiality, privacy, and safety rules. Participants will be asked not to disclose information shared by other group members outside the session and may use a preferred first name or pseudonym during calls. They will also be instructed to join the sessions from a private location whenever possible and to use headphones. Each weekly multiconference session will follow a standardized 30-minute structure: a 5-minute check-in, a 10-minute review of completed homework, a 10-minute feedback segment, and a 5-minute wrap-up. Throughout the five sessions, positive or corrective feedback will be delivered in accordance with Miltenberger’s guidelines (51) after reviewing the completed homework. Feedback should be provided immediately after the target behavior and include descriptive praise for correct performance or effort. Corrective feedback should be non-negative, focus on improvement, address one aspect of behavior at a time, and be preceded by praise. Participants will also be encouraged to support one another throughout the change process. Facilitators will be responsible for maintaining time equity, preserving the structured behavioral focus of the session, managing participant interaction around app-based tasks, and ensuring that confidentiality, privacy, and safety rules are followed. If severe distress, suicide risk, trauma-related disclosure, or interpersonal conflict emerges during a call, the facilitator will redirect the group process and activate the Crisis Disclosure Protocol, including private follow-up and referral or emergency procedures when necessary.

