#### Outcome measures

2.2.7

Participants will be assessed at three key time points: pre-intervention (T1), post-intervention (T2), and six-month follow-up (T3), using the instruments listed in **Table 2**. The evaluated variables will include sociodemographic, academic, and clinical characteristics; presence of mental disorders; emotional well-being; psychological, emotional and social well-being; positive emotion; engagement; relationships; meaning; accomplishment; treatment adherence and dropouts; and satisfaction with the intervention, following the same order presented in **Table 2** and **Figure 1**. All evaluations will be conducted in person by independent psychologists blinded to the study’s objectives, hypotheses, intervention conditions, and group assignments. Evaluator training will be provided by two senior psychologists with extensive experience in psychological assessment and intervention studies, consisting of 20 hours of theoretical and practical seminars, including role-playing scenarios and supervised mock assessments to ensure standardized administration of the instrument. A random sample of 10% of the screening interviews will be audio-recorded and independently rated by a second independent blinded psychologist. Interrater agreement for the final eligibility decision (eligible vs. excluded) will be calculated using Cohen’s kappa, with κ ≥.80 considered the minimum acceptable threshold. Any discrepancies will be resolved by consensus with the senior supervisors.

**Table 2 T2:** Variables, measurement instruments, and administration format.

Variable	Measurement instrument	Administration format
Sociodemographic, academic and clinical characteristics	Sociodemographic, academic, and clinical questionnaire	Hetero-administered
Mental disorders	Structured Clinical Interview for DSM-5, Clinician Version (SCID-5-CV; First et al., 2015)	Hetero-administered
Primary outcomes		
Emotional well-being	Warwick–Edinburgh Mental Well-Being Scale (WEMWBS; Tennant et al., 2007)	Self-administered
Psychological, emotional, and social well-being	Mental Health Continuum–Short Form (MHC-SF; Keyes, 2002)	Self-administered
Secondary outcomes		
Positive emotion	Positive and Negative Affect Schedule (PANAS; Watson et al., 1988)	Self-administered
Engagement	Utrecht Work Engagement Scale–Student Version (UWES-S; Schaufeli & Bakker, 2003)	Self-administered
Relationships	Social Connectedness Scale (SCS; Lee & Robbins, 1995)	Self-administered

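### The safety trigger stated for the T1–T3 assessments covers only active suicidal behaviors, although suicide risk and acute distress are what is assessed

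*Protocol article*

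**What the plan says.** Section 2.2.5 (Ethics) sets the scope of the screening: "Suicide risk and acute distress will be assessed at each assessment point (T1, T2, and T3"), with the C-SSRS Screen Version as the instrument. It then gives the entry condition: "Positive responses indicating active suicidal behaviors will trigger the study safety protocol". The triggered protocol consists of a short risk assessment by a psychologist, referral where needed, and "exclusion or discontinuation from the intervention when acute risk is identified".

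The same section adds a periodic check: "Safety data and distress-related dropouts will be monitored monthly by the two senior clinical psychology supervisors". It also provides for adverse event reporting to the ethics committee and a standing help section in the app, and states that the app raises no automated alerts.

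Section 2.2.6.2 has a separate rule for the PPIA+M group calls. It begins "If severe distress, suicide risk, trauma-related disclosure, or interpersonal conflict emerges during a call" and leads to private follow-up, with referral or emergency procedures when necessary.

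Section 2.2.7 says who carries out the assessments: "All evaluations will be conducted in person by independent psychologists", blinded to group.

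**The concern.** The article names two things to be assessed, suicide risk and acute distress, and attaches a response to only part of the first. A positive screen that falls short of active suicidal behavior meets no stated condition for action, and neither does acute distress.

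The matter at stake is participant safety. The response in section 2.2.5 is graded: a risk assessment comes first, and removal from the intervention is kept for acute risk. If only behavior opens that sequence, the step meant to find out whether the risk is acute is not required for people who report risk without behavior. The sample size, error rates and primary analysis are unaffected.

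**Working it through.** No plan figure needs to be reproduced, because the point is one of wording. The check sets the relevant provisions side by side and asks, for each, whether it gives a stated individual response at T2 or T3 to (a) suicide risk without active suicidal behavior, or (b) acute distress.

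| Provision | Where it applies | Covers (a)? | Covers (b)? |
|---|---|---|---|
| Safety protocol trigger, 2.2.5 | All arms, T1–T3 | Not as worded | Not as worded |
| Discontinuation for acute risk, 2.2.5 | A step inside the triggered protocol | No separate entry | No separate entry |
| Monthly review by senior supervisors, 2.2.5 | Whole trial | Periodic oversight, not an individual response | Same |
| Help section in the app, 2.2.5 | App users; the waiting list gets the app only after final follow-up (2.2.6.3) | Passive | Passive |
| Crisis Disclosure Protocol, 2.2.6.2 | PPIA+M, during calls only | Yes, on a call | Yes, on a call, if severe |
| SCID-5-CV, which covers suicidality, 2.2.1 and 2.2.7.2 | Initial eligibility assessment | Not stated for T2 or T3 | Not stated for T2 or T3 |
| In-person psychologist evaluator, 2.2.7 | All arms, T1–T3 | Discretion, no stated rule | Discretion, no stated rule |

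The only provision broad enough to cover both cases is the one for calls. It does not apply at the assessment visits, and the PPIA and waiting list arms have no calls. Suicide risk voiced on a call therefore has a stated response, while the same risk reported on the trial's dedicated screen has one only if it is read as active suicidal behavior.

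Exposure, from the figures in section 2.2.4:

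- Participants under the section 2.2.5 rule: 3 arms × 59 = 177.
- Planned post-randomization screens (T2 and T3): 2 × 177 = 354.
- If only the analytical sample attends both visits: 2 × 141 = 282.

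The documents give no rate of suicide risk or acute distress short of active behavior, so the number of participants affected cannot be computed.

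**The case against.** The strongest reply is that the article only summarizes the safety protocol. Response levels on a screening scale are operational detail that a journal article may leave to the full document, and that document may set finer levels. Section 2.2.5 does not say that behavior is the only trigger. It does not define active suicidal behaviors or list the C-SSRS items. Its graded response, in which some triggered cases turn out not to be acute, would also fit a broader use of the phrase. Every assessment is done in person by a trained psychologist, the study is bound to professional ethical principles, and an ethics committee has approved it.

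Much of this stands as a limit on the claim. It does not remove the claim, because the article is not silent: it states an entry condition, and that condition is narrower than the assessment announced in the sentence before it and narrower than the article's own wording for calls.

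Three stronger readings are tempting and are not supported:

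- **Participants at risk will go without care.** The safety protocol is not shown and psychologists see everyone in person, so a gap in actual care is not demonstrated.
- **The T1 trigger is idle because it repeats an exclusion criterion.** Section 2.2.2 does exclude "dissociative disorders, active substance dependence, or active suicidal behaviors", but overlap is no fault: the trigger still gives an excluded student a risk assessment and referral. The SCID-5-CV also covers suicidality at that visit.
- **The 354 screens measure the size of the problem.** They count how often the rule applies, not how often it fails.

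**Conclusion.** The point holds as a defect in the stated trigger. Read literally, section 2.2.5 gives no individual response at T2 or T3 to a participant in any arm who reports suicide risk without active suicidal behavior or who shows acute distress. Such a case is left to the evaluator's discretion, the monthly review and, for app users, a passive help section.

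The conclusion rests on two assumptions: that active suicidal behaviors carries its ordinary, narrower meaning, and that staff follow the published wording. If the unseen safety protocol already acts on suicide risk and distress more broadly, the defect is confined to the article's wording. Confidence is medium for that reason. Because the point concerns safety and is cheap to correct, the sponsor should correct it.

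**What to change.** Reword the trigger in section 2.2.5 along these lines: any positive C-SSRS response indicating suicide risk, whether or not active suicidal behavior is present, or severe or acute distress noted by the evaluator, starts the brief psychologist risk assessment, in all three arms and at T1, T2 and T3. Referral follows as needed, and exclusion or discontinuation stays reserved for acute risk. This brings the assessment visits into line with section 2.2.6.2 for suicide risk and distress. Distress should be named separately, because section 2.2.5 gives no instrument for it other than the C-SSRS.

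The change needs no new visit or instrument. It will add some brief risk assessments, in a number the documents do not allow one to estimate, and it may need ethics committee approval if judged a substantial modification.

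A clerical edit can go with it: the C-SSRS is missing from Table 2 and from the list in section 2.2.7 that opens "The evaluated variables will include sociodemographic, academic, and clinical characteristics; presence of mental disorders; emotional well-being". Its use and timing are already clear from section 2.2.5, and the SPIRIT figure is not shown here, so nothing turns on this.

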#### Interventions

2.2.6

A standardized, manualized intervention protocol will be developed for each experimental condition to ensure internal validity, consistency across delivery formats, and adherence to theoretical fidelity. The full intervention manual, including module outlines, facilitator guidance, fidelity and adherence checklists, and operational app-related materials, will be made available to independent researchers upon reasonable request once the trial is completed, subject to institutional and ethical restrictions.

Participants will be randomly assigned to one of three groups: (a) PPIA, a psychological intervention based on the PERMA model delivered via a mobile app; (b) PPIA+M, the same PERMA-based intervention delivered via app and supplemented with weekly telephone-based multiconference support sessions; and (c) WLCG (Waitlist Control Group), in which participants will not receive any intervention during the study period but will be granted access to the mobile intervention after completing all post-assessments. Although the intervention is grounded in positive psychology and the PERMA model, it integrates cognitive-behavioral principles such as structured goal setting, behavioral self-monitoring, action planning, and homework-based skill practice, which justify its classification as a CBT-informed intervention.

The two experimental conditions will consist of five modules, each corresponding to one of the five components of the PERMA model. Each module will last approximately 45 minutes and will be completed across one-week, engaging participants in three to five brief experiential and reflective activities per module (approximately 5–10 minutes per task). Content will be distributed across the week, and daily adherence will be encouraged through app notifications and visual progress tracking. In both intervention arms, task completion and engagement metrics will be automatically recorded by the app.

The intervention will be administered by licensed psychologists or doctoral students in clinical psychology with prior experience in digital and group interventions. The PPIA app will be entirely self-administered by participants, requiring no direct facilitation. In contrast, the multiconference sessions in the PPIA+M group will be administered by licensed psychologists or doctoral students in clinical psychology. These facilitators will undergo approximately 70 hours of structured training delivered by three senior clinical researchers with 20 to 35 years of experience in psychological therapies. The training will combine theoretical and practical seminars, a detailed review of intervention manuals, and extensive role-playing exercises to simulate delivery scenarios. The senior researchers responsible for the training will evaluate the facilitators’ adherence to the manuals and competence in group management, and will provide weekly supervision and feedback.

Following facilitator training and before conducting the randomized controlled trial, an internal pilot study will be carried out in which each facilitator will apply the intervention to approximately 15 participants. The objectives of the pilot are to review the acceptability and clarity of the intervention materials, evaluate the usability of the mobile application, and identify any procedural or technical challenges requiring refinement. Facilitator adherence to the manuals and delivery protocols will be assessed using structured observation checklists, and concordance of delivery and scoring among facilitators will be examined using Cohen’s kappa indices. In the PPIA+M arm, all multiconference sessions will be audio-recorded (with participant consent) and reviewed by the professionals responsible for facilitator training. These professionals will supervise facilitators weekly, evaluate their adherence to the manuals, assess their delivery skills, and provide corrective feedback where necessary.

Once the pilot data have been analyzed and refinements incorporated, recruitment for the full randomized controlled trial will commence following the procedures described in the Recruitment section. To maintain delivery quality and fidelity, facilitators will attend weekly 60-minute supervision meetings with the principal investigator and clinical coordinators. Supervision will involve case reviews, adherence monitoring, and problem-solving. Fidelity will be monitored using structured binary checklists assessing three core domains: adherence to PERMA content, competence in delivering Miltenberger-based feedback, and time management/group boundary control. A random sample of 20% of telephone sessions per facilitator will be independently rated by two raters using audio-recordings. Cohen’s kappa will be used to assess inter-rater agreement for the binary fidelity items. Acceptable fidelity will be defined as ≥80% adherence; if a facilitator falls below this threshold, targeted corrective supervision will be provided and the subsequent session will be monitored. Aggregated fidelity compliance scores and inter-rater reliability metrics will be reported in the final trial publication.

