A growing body of research has demonstrated the efficacy of interventions rooted in positive psychology for promoting mental health and well-being among young adults, particularly when delivered through mobile applications. For example, Bendtsen et al. (28) conducted a randomized controlled trial evaluating the impact of a positive psychology–based intervention delivered via a mobile health (mHealth) application. Compared to a control group that received only online mental health information, the intervention group showed significant improvements in positive mental health and reductions in anxiety and depression symptoms at the six-month follow-up. Similarly, Mak et al. (29) compared the effectiveness of basic mindfulness and Health Action Process Approach (HAPA)-enhanced mindfulness programs with a waitlist control group. Both intervention groups demonstrated significant improvements in psychological well-being, which were sustained at the three-month follow-up. However, it´s important to note that none of the reviewed interventions was based on the PERMA model (20). Moreover, a key issue identified in both studies is low adherence rates; Bendtsen et al. (28) reported that participants completed an average of only 2.8 out of 6 planned sessions, highlighting a significant adherence challenge; similarly, Mak et al. (29) noted that just 55% of participants completed the full three-month intervention.

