Meaning	Meaning in Life Questionnaire (MLQ; Steger et al., 2006)	Self-administered
Accomplishment	Achievement Goal Questionnaire–Revised (AGQ-R; Elliot & Murayama, 2008)	Self-administered
Satisfaction with the intervention	Satisfaction with the intervention: Client Satisfaction Questionnaire–8 (CSQ-8; Larsen et al., 1979; Vázquez et al., 2019, Spanish version)	Self-administered
Treatment adherence and dropouts	Recording of the number of modules completed, between-session tasks performed, attendance at the weekly 30-minute multiconference sessions, and dropouts and time	Hetero-administered

SCID-5-CV, Structured Clinical Interview for DSM-5 Disorders, Clinician Version; WEMWBS, Warwick–Edinburgh Mental Well-Being Scale; MHC-SF, Mental Health Continuum–Short Form; PANAS, Positive and Negative Affect Schedule; UWES-S, Utrecht Work Engagement Scale–Student Version; SCS, Social Connectedness Scale; MLQ, Meaning in Life Questionnaire; AGQ-R, Achievement Goal Questionnaire–Revised; CSQ-8, Client Satisfaction Questionnaire–8.

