##### Treatment adherence and dropouts

2.2.7.5

Throughout the study, information on participant dropouts will be systematically recorded, including the time point of withdrawal (T1, T2, or T3) and the stated reasons for discontinuation when available. Treatment adherence will be evaluated by tracking the number of modules completed within the mobile app and the between-session tasks performed by each participant (e.g., experiential exercises, reflections, and homework activities). For participants in the PPIA+M condition, adherence will also include attendance at the weekly 30-minute multiconference sessions. App data logs will automatically capture completion rates and activity engagement, while facilitators will maintain attendance and participation records for the multiconference sessions.

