#### Statistical analyses

2.2.9

Statistical analyses will be conducted using SPSS version 29.0 and R software (62), following the intention-to-treat (ITT) principle. All randomized participants will be analyzed in the groups to which they were assigned (PPIA, PPIA+M, WLCG), regardless of intervention adherence or dropout.

Missing data will be handled using multiple imputation by chained equations (MICE).

The imputation model will include the following predictors: sociodemographic characteristics (sex, gender identity, age, marital status, living arrangements, rural/urban setting, employment status, and self-reported socioeconomic level), academic variables (current academic program, year of enrolment), clinical characteristics (having initiated psychological or psychopharmacological treatment within the two months prior to the study, currently participating in another mental health–related research study), and baseline scores on the primary outcomes (emotional well-being and psychological, emotional, and social well-being).

To analyze the effect of the intervention on the primary outcome, psychological well-being, operationalized through two co-primary measures—global positive mental well-being assessed with the WEMWBS and emotional, psychological, and social well-being assessed with the MHC-SF—separate Linear Mixed Models (LMMs) will be conducted for each co-primary outcome using Restricted Maximum Likelihood (REML) estimation, with fixed effects for group, time, and the group-by-time interaction. Time will be treated as a categorical factor with three levels (T1: baseline, T2: post-intervention, T3: six-month follow-up), and random intercepts will be included to account for intra-subject variability. The baseline assessment (T1) will be modeled as part of the repeated outcome vector rather than as a separate baseline covariate. Random slopes for time will not be included in the primary models.

Model assumptions, including the normality and homoscedasticity of residuals, will be evaluated using Q-Q plots and residual-versus-predicted scatterplots before final model interpretation.

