However, some limitations should be acknowledged. First, the sample will be drawn from a single university, which may limit the generalizability of the findings to other academic or cultural contexts, and participation will be voluntary, raising the possibility of self-selection bias. Voluntary enrollment may attract students with higher baseline motivation, greater interest in psychological well-being, or greater readiness to engage in self-guided activities. Second, outcomes will rely primarily on self-report measures, which may be subject to social desirability bias, reporting biases, and measurement fatigue across repeated assessments. Third, the use of a waiting list control group, while ethically and practically justified, may lead to an overestimation of intervention effects compared with active control conditions. Moreover, this passive comparator does not allow the specific active ingredients of the PERMA model to be isolated from non-specific factors such as digital novelty, participant expectancy, structured self-monitoring, or human support. Therefore, any efficacy findings should be interpreted as supporting the effectiveness of the intervention package relative to no immediate intervention, rather than demonstrating the specific incremental value of the PERMA components alone. Fourth, adherence is expected to play a critical role in determining intervention effectiveness, particularly in self-guided digital formats. Because telephone multiconference support will be delivered in small groups and facilitated by trained psychologists, minor peer-group or facilitator effects cannot be completely ruled out. Although these effects are expected to be limited because the sessions are brief, manualized, and focused on adherence feedback rather than group psychotherapy, they should nevertheless be considered when interpreting differences between PPIA and PPIA+M. Future studies should replicate these findings using multisite samples, active comparators, and complementary assessment strategies.

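### The stated imputation predictors are all baseline items, so imputed T2 and T3 scores ignore app use and call attendance, which are recorded for dropouts too

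*Protocol article*

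**What the plan says.** On collection, section 2.2.6 states: "In both intervention arms, task completion and engagement metrics will be automatically recorded by the app". Section 2.2.7.5 says "Treatment adherence will be evaluated by tracking the number of modules completed within the mobile app" and "App data logs will automatically capture completion rates and activity engagement"; it also has facilitators keep attendance records for the calls. Table 2 sums this up as "Recording of the number of modules completed, between-session tasks performed, attendance at the weekly 30-minute multiconference sessions, and dropouts and time".

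On analysis, section 2.2.9 keeps every randomized student in the assigned group and handles missing data by chained-equations imputation. It then itemizes: "The imputation model will include the following predictors: sociodemographic characteristics", followed by academic variables, clinical eligibility items and the baseline WEMWBS and MHC-SF scores. It names no module count, task count, call attendance, arm or post-baseline score.

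On the role of adherence, the Discussion says "adherence is expected to play a critical role in determining intervention effectiveness, particularly in self-guided digital formats". The Introduction reports that in an earlier app trial "participants completed an average of only 2.8 out of 6 planned sessions". In section 2.2.9.2 adherence appears only as an exploratory moderator.

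**The concern.** A variable is worth having in an imputation model when it predicts the missing score and also predicts whether the score is missing. By the protocol's own account, adherence should predict the score. It may well predict missed visits too, since a student who stops using the app may also stop attending. Because the app and the facilitators record adherence, it should be known for the very students whose T2 or T3 score is absent.

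With a baseline-only list, two students with the same baseline profile draw from the same imputation distribution whether one opened a single module or finished all five. Missing at random given baseline alone is then a harder assumption than it needs to be. At stake are the comparisons of each active arm with the waiting list, and PPIA+M against PPIA, because the calls are meant to change adherence.

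The list is specific enough to count as a decision rather than a detail left for later. It goes down to marital status and rural or urban setting. It even includes recent treatment start and participation in another study, which are exclusion criteria in section 2.2.2 and so should hardly vary among randomized students.

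**Working it through.** **The plan's own figures.** For the sample size, the noncentrality is f² × N × m / (1 − ρ) = 0.16² × 141 × 3 / 0.5 = 21.66, with 4 and 276 degrees of freedom and α = .025. Power comes to 0.9510 (stated .9509). 141 / 0.8 = 176.25, rounded up to 177, or 59 per arm. Both figures reproduce, and nothing below changes them.

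**Inputs from the protocol.** Attrition 20%, correlation .50, standardized effect 0.32 (all section 2.2.4).

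**Assumptions not in the protocol.** The true effect over all randomized students is 0.32 SD in each active arm. A share of active-arm students (30% or 50%) are low users, who gain one fifth of what high users gain. Low users are 1, 2 or 4 times as likely to miss T2. Attrition is equal across arms.

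**Step 1: arm in the imputation model, use left out.** Dropouts receive the mean effect of the observed students in their arm, so the estimate equals that mean. Take 30% low users and a ratio of 4:
- High-user effect: 0.32 / (0.7 + 0.2 × 0.3) = 0.421. Low-user effect: 0.2 × 0.421 = 0.084.
- Missing probability: 0.2 / (0.7 + 4 × 0.3) = 0.105 for high users and 0.421 for low users.
- Low users among the observed: 0.3 × 0.579 / 0.8 = 0.217.
- Estimate: 0.217 × 0.084 + 0.783 × 0.421 = 0.348, an excess of 0.028.

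The same steps give the other cases. The last two columns are mean estimates from 800 simulated trials of 59 per arm with 10 imputations (Monte Carlo standard error about 0.006).

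| Low users | Ratio | Arm, no use (formula) | Arm, no use (simulated) | Arm plus use (simulated) |
|---|---|---|---|---|
| 30% | 1 | 0.320 | 0.319 | 0.318 |
| 30% | 2 | 0.334 | 0.330 | 0.316 |
| 30% | 4 | 0.348 | 0.349 | 0.322 |
| 50% | 1 | 0.320 | 0.316 | 0.317 |
| 50% | 2 | 0.338 | 0.337 | 0.320 |
| 50% | 4 | 0.352 | 0.342 | 0.312 |

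The excess is about 0.01-0.03 SD and vanishes at a ratio of 1. At 40% attrition the simulated estimates for ratios 2 and 4 are 0.36-0.40 without use and about 0.32 with it.

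**Step 2: a steeper use model.** Here the effect is proportional to modules completed, with mean use 2.33 of 5 (2.8 / 6 × 5) or 3.5, and dropout falls with use. With arm but no use the estimate is 0.34-0.38, an excess of 0.02-0.06 SD. With the module count added it is 0.32.

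**Step 3: the list read literally, without arm.** Missing scores in every arm are drawn from the same pooled distribution given baseline, so the imputed 20% contributes no difference between arms. The estimate is (1 − 0.2) times the observed-student effect:
- dropout unrelated to use: 0.8 × 0.32 = 0.256 (simulated 0.251-0.254);
- ratio 4 with 30% low users: 0.8 × 0.348 = 0.278 (simulated 0.279);
- upper end of Step 2: 0.8 × 0.38 = 0.304.

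Omitting arm therefore removes 0.2 × 0.32 = 0.064 to 0.2 × 0.38 = 0.076. Omitting use adds 0.01-0.06 when low users drop out more. The two errors partly cancel, so the literal list is furthest off when use is unrelated to dropout.

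**Step 4: PPIA+M against PPIA.** If mean use is 3.5 against 2.33 modules and attrition 15% against 25%, the true difference is 0.32 × 3.5 / 2.33 − 0.32 = 0.16. The estimate is 0.13 with the stated list, 0.145 with arm added, and 0.16 with arm and modules.

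**The case against.** The strongest reply is that a reader might infer that the plan credits a student who quit after one module with the benefit of those who stayed. The text does not support that. It describes a model containing arm, and the list does not name arm. Read literally, the dropout is imputed from students of all three arms and the contrast is diluted, not inflated. Step 3 confirms this, and that error belongs to the omission of arm. Restoring 0.32 by adding only the module count to the listed items is weak evidence too, because a count set to 0 in the waiting list partly stands in for arm.

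Second, no section says that missing scores come mainly from low users. The Discussion ties adherence to effectiveness, not to missed visits. Assessments are in person, and section 2.1 plans reminders and follow-up of missing data. The low use cited in the Introduction is from earlier trials and is not a forecast for this one. This stands, so the bias is conditional.

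Third, the size is modest: 0.06 SD is at most 0.06 / 0.204 = 0.29 of the contrast's sampling SD at 59 per arm. This also stands.

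Fourth, the article does not say the list is exclusive, and a fuller plan could add auxiliary variables. But so detailed a list will be taken as the specification, and nothing in it points to use data. Chained equations might carry a T2 score into a missing T3 score, but the text does not say so, and this would not help a student missing both.

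Finally, the mixed model would ignore use as well, since it holds only group, time and their interaction. That use is measured after randomization is no obstacle, because it would enter the imputation only and the intention-to-treat comparison would not change.

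**Conclusion.** The point holds in a limited form. The stated imputation model leaves out use and attendance data that the trial collects independently of the visits and that the protocol itself considers central to effectiveness. That such logs exist for students who miss T2 or T3 is an inference from automatic recording, but a sound one.

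With arm in the model, the cost of the omission at 20% attrition is an overstatement of about 0.01-0.06 SD in the active-versus-waiting-list contrast at T2. This requires that low users both benefit less and miss visits more. If dropout is unrelated to use, there is no cost. The list as written also omits arm, which is the larger error and acts in the opposite direction, giving about 0.25-0.30 for a true 0.32. Adding arm alone would leave the upward error exposed, so both should be corrected together.

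A reader might go on to infer that the confirmatory result is biased. That has not been shown: the calculations cover pairwise contrasts at T2, not the three-group group-by-time test over T1 to T3, and T3 was not examined. This is a worthwhile improvement rather than a threat to the trial.

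**What to change.** In section 2.2.9, extend the imputation predictors with trial arm, the number of modules completed by the visit (0-5, set to 0 in the waiting list) and, for PPIA+M, the number of calls attended (0-5). Use arm-specific terms or impute within arm. State that use and attendance are auxiliary variables in the imputation only, and leave the mixed model, contrasts and significance thresholds unchanged.

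The cost is a sentence or two of text and a slightly larger imputation model. No new data, participants or staff are needed. In an arm-aware model at 59 per arm, the SD of the contrast was 0.204 with and without the module count. Imputing within arms with many covariates may cost a little precision: with 20 extra covariates the SD rose from 0.213 to 0.223. Arm-specific terms in one pooled model, or a shorter covariate list, may limit that loss, though neither was tested. Call attendance as a predictor was not simulated either.
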